### 2.13 Economic evaluation

An economic evaluation will be conducted from the healthcare system perspective. Health outcomes captured through the AQoL-8D will be evaluated using Quality Adjusted Life Years (QALYs). Intervention and resulting costs per patient in the enhanced CBT group will be compared against those in the standard CBT group, and include acute care, primary care, mental health care, community care, and medication use. Data collected using the Use of Care Services survey will be supplemented with linked, individual-level Admitted Patient data, Emergency Department data and Mental Health Ambulatory data, along with Australian Government data from the Medicare Benefit Schedule (MBS) and Pharmaceutical Benefit Scheme (PBS). A cost-utility analysis will compare differences in QALYs with differences in resource use, and will be presented using an incremental cost utility ratio. This will provide a basis to make judgements on whether the enhanced CBT is cost-effective given to the price that Australian Government funders are likely willing to pay for a QALY for the target population [39]. The *iMTA Productivity Cost Questionnaire* [36] with the Australian Community Participation Questionnaire [33] will be used to estimate the value of social contributions.

### 2.14 Oversight and monitoring

#### 2.14.1 Data monitoring, harm, and auditing

Data management will be overseen by an independent data safety and monitoring board (DSMB) comprising a biostatistician, clinical trial expert, and health information systems expert. The DSMB committee will provide their expertise and recommendations to the research group. The primary responsibilities of the DSMB are to 1) periodically review and evaluate the accumulated study data for participant safety and progress, and, when appropriate, efficacy, and 2) make recommendations to the research group concerning the continuation, modification, or termination of the trial. In addition, a clinical advisory committee including a geriatric psychiatrist, clinical psychologist and consumer advocates will meet prior to, and six-monthly, for the trial duration. The CIs will report to the independent DSMB on all adverse events, as well as to the Ethics committee.

#### 2.14.2 Adverse events reporting

Any adverse events or clinical complications that arise as result of the therapeutic product offered will be reported by clinicians, managers, and research assistants to CIs during regular project supervision. All adverse events will be documented and reported in the trial outcomes, and the Independent Advisory and Data Safety Boards will be informed. All serious adverse events will be reported to the HRECs within 72 hours. The reports will be followed by a detailed written report. Follow-up reports will identify a participant by their unique code.

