### 2.5 Interventions

Both the standard and enhanced CBT programs are guided by structured manuals for therapists and supported by workbooks containing homework exercises and lesson summaries for participants. In both treatment conditions, sessions will be run by clinical psychologists and provisional psychologists trained in delivery of the treatment protocols. To control for therapist differences, all therapists will be trained in and will conduct both treatments (allocated randomly). Supervision will be provided by chief investigators (CIs) and associate investigators (AIs) with treatment adherence and differentiation between conditions as a core focus. All therapy sessions will be recorded, and a random 20% will be rated by an independent expert unaware of the study hypotheses for adherence to the therapeutic manual using a codebook and form based on Waltz, Addis, Koerner, & Jacobson [26]. Therapy alliance will be measured using the 19-item Helping Alliance Questionnaire [HAq-II; 27].

The standard program will comprise our empirically validated CBT program for older age anxiety and depression, *Ageing Wisely*. The *Ageing Wisely* program consists of 12 weekly individual one-hour sessions to teach practical skills to help manage anxiety and depression including: goal setting, activity scheduling, problem solving, graded exposure, cognitive restructuring, and sleep hygiene. Skills such as assertive communication training, as well as examples that illustrate application of CBT skills to increase social connections, were not included in the standard CBT program. Homework activities are assigned to promote skill acquisition and generalisation.

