### 2.12 Statistical methods

Data will be analysed using intention-to-treat principles. All participants will be included in analyses based on the condition to which they were initially allocated. Multiple imputation will be used to manage missing data. The efficacy of the programs will be established using mixed model analysis to compare the mean differences in clinical diagnostic severity (established by clinicians who are blind to treatment allocation) and scores on self-report measures at pre-treatment, post-treatment, and at a 12-month follow-up period.

Analysis will be a mixed model with random subject effect, fixed effects relating to group allocation (between-group), time (within-subject) and covariates. Interaction contrasts will be used if the time x group interaction reaches statistical significance, but the main effect contrast will be used if not.

Statistical inference will be based on the nonparametric bootstrap if the assumption of Normality is violated. The same process will be used for the secondary hypotheses to compare the groups on all outcome measures. Differences between groups in baseline characteristics, and therapy factors (e.g., sessions attended, therapist alliance) will be examined and controlled for in analyses.

In addition, an economic evaluation will be undertaken to measure the relative benefit in health outcomes and resource use for the enhanced intervention compared to standard CBT. Moderation analyses will examine the impact of moderators on treatment outcomes.

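### Section 2.14.2 words staff reporting as therapy-related events only, which is narrower than the promise to document and report all adverse events

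*Protocol article*

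**What the plan says.** Section 2.14.2 of the protocol article describes how staff pass events upward: "Any adverse events or clinical complications that arise as result of the therapeutic product offered will be reported by clinicians, managers, and research assistants", and they do so "to CIs during regular project supervision". The sentence that follows has no causal limit: "All adverse events will be documented and reported in the trial outcomes". Serious events have no causal limit either: "All serious adverse events will be reported to the HRECs within 72 hours".

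Section 2.14.1 repeats the wide scope: "The CIs will report to the independent DSMB on all adverse events, as well as to the Ethics committee". It also gives the DSMB the task to "periodically review and evaluate the accumulated study data for participant safety and progress, and, when appropriate, efficacy" and to recommend whether the trial continues, changes or stops.

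Two other places bear on the point. Section 2.5 has every therapist deliver both programmes, so the treating clinicians, who are among the named reporters, know each participant's arm. Section 2.10 says that reasons for withdrawal will be gathered where possible, partly so that adverse events are reported correctly.

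**The concern.** The chief investigators can pass on only what reaches them. If staff are asked to report only events that they believe the therapy caused, events put down to age, physical illness or the underlying disorder may stop at the first step. The later promises could then not be met in full, whatever the investigators intend.

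The population makes this more than a drafting matter. Participants are 65 or older with anxiety or depressive disorders, and Section 1.1 itself links these conditions, through isolation and loneliness, to self-harm and death. Deterioration or an admission in such a person is easily attributed to something other than a talking therapy. At stake are the completeness of the adverse-event record that the DSMB uses and of the harms reported at the end. A secondary risk is that the judgement differs by arm, because some of those making it know the allocation.

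**Working it through.** No figure in the protocol bears on adverse events, so there is nothing to reproduce. The main check sets the stated scopes side by side.

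- Staff to chief investigators (2.14.2, first sentence): events or complications arising from the therapy.
- Documentation and trial report (2.14.2, second sentence): all adverse events.
- DSMB and ethics committee (2.14.1): all adverse events.
- Ethics committees, within 72 hours (2.14.2): all serious adverse events.

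The first is the main reporting route described, and it is the only one of the four with a causal condition. The other three are unrestricted. The only other route named for adverse events is the collection of withdrawal reasons in Section 2.10, which reaches only those who withdraw. The text does not say who judges causality, whether that person is blind, or how an event judged unrelated would reach the chief investigators.

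The second check asks what such a filter could do to the counts. The arm size of 86 comes from Section 2.7. The event risk and the attribution shares are assumptions, because the documents give none.

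Formulas, for a true risk *p* that is equal in both arms and an attributed share *a* in each arm:

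- expected reported events per arm = 86 × *p* × *a*
- apparent risk ratio = *a*(enhanced) / *a*(standard)
- apparent risk difference = *p* × (*a*(enhanced) − *a*(standard))

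Results for *p* from 10% to 30%:

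- No filter (*a* = 1 in both arms): 86 × 0.10 = 8.6 to 86 × 0.30 = 25.8 events per arm.
- Equal filter (30% in both arms): 86 × 0.10 × 0.30 = 2.6 to 86 × 0.30 × 0.30 = 7.7 events per arm. The risk ratio is 1.0 and the risk difference is 0.
- Unequal filter (50% enhanced, 30% standard): 4.3 against 2.6 events at *p* = 10%, and 12.9 against 7.7 at *p* = 30%. The risk ratio is 0.50 / 0.30 = 1.67 and the risk difference is 0.20 × *p*, that is +2 to +6 percentage points.
- The same shares reversed: the risk ratio is 0.30 / 0.50 = 0.60 and the risk difference is −2 to −6 points.

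The ratios follow entirely from the assumed shares. The illustration shows direction only: a filter on cause always lowers the count, but creates a false difference only if it acts differently in the two arms.

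**The case against.** The best defence is that this is loose wording and not a decision to leave events out. The causal clause can be read as attached to clinical complications alone, and the next sentence says that all adverse events will be documented. That reading is possible, so a definite exclusion of unrelated events is not established. The scope still needs to be stated once and consistently, because staff following the other natural reading would report less.

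Several stronger conclusions might be inferred, and the documents do not support them.

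- *Worsening, suicidal ideation or admissions would go unrecorded.* They are collected in both arms by other means: the ADIS-5 by blinded assessors, the GAI, GDS and DSI-S, the Use of Care Services survey and linked records. What is missing is any statement that these data feed adverse-event reporting. The DSMB reviews accumulated study data, so its view is not shown to be confined to staff reports.
- *Serious events are filtered too.* The sentence on serious events has no causal limit.
- *Events after the 12 sessions have no route.* Nothing says that project supervision ends with therapy, the named reporters include managers and research assistants, and Section 2.10 keeps participants in follow-up.
- *All reporters are unblinded.* This is secure only for therapists. The position of managers and research assistants is unclear.
- *The safety comparison is biased.* No between-arm comparison of adverse events is described. The sentence "The same process will be used for the secondary hypotheses to compare the groups on all outcome measures" concerns outcome measures, and no adverse-event measure is among them. Having the same therapists in both arms also removes differences between therapist pools, though not judgements that depend on the arm.

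It is also fair that event definitions, causality scales and forms usually sit in the full protocol, which is not shown. Their absence from an article is not a finding. The point here is different: the article states a scope and then contradicts it.

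**Conclusion.** The point holds as an inconsistency of scope between the first sentence of Section 2.14.2 and the unrestricted promises in Sections 2.14.1 and 2.14.2. Read as written, the staff rule would supply less than the plan says the DSMB, the ethics committee and the trial report will receive.

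Under-counting is the direct risk. A difference by arm is possible because therapists know the allocation, but it requires unequal attribution, which the documents neither state nor rule out. The size is unknown, because no event rates or attribution rates are given. The primary efficacy analysis is not affected. The correction is worth making because it is cheap and strengthens safety monitoring.

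**What to change.** Replace the first sentence of Section 2.14.2 with wording such as: *All adverse events in both arms, from randomisation to T3, are reported to the chief investigators regardless of suspected cause. Relatedness to the intervention is rated afterwards and recorded as a separate field.* The promises in Sections 2.14.1 and 2.14.2 can then stand unchanged.

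Optionally, state that reported events will be cross-checked against admissions already collected through the Use of Care Services survey and the linked data. This supplements direct reporting and cannot replace it. The survey looks back six months, so at T3 it reaches only to about month 6 after the start of therapy, while T2 falls 14 weeks after baseline. The linked records cover only participants who consent to linkage.

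The cost is a protocol wording change, a higher recorded event count and slightly more form completion. The optional cross-check uses data that the trial already plans to hold.

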#### 2.14.3 Ethics and dissemination

This study has been approved by the Macquarie University Human Research Ethics Committee (Reference: 5201938336887; approved 24/01/2019), the NSW Population & Health Services Research Ethics Committee (PHSREC) (Reference: 2019/ETH12532), and the External Request Evaluation Committee (EREC) (Reference: RMS0283) within the Australian Department of Human Services. Changes to the trial will be submitted as amendments. See section ‘Data Management’ for information on consent, confidentiality, and access to data. The results of the study will be disseminated in peer-reviewed journals and presented at (inter)national conferences. Results will be reported on institutional websites and consumer-based websites. In all cases, only deidentified data will be used, and summary statistics will be reported. No information identifying individual participants or sites of service delivery, will be reported. Study records will be retained for a minimum of 15 years after the last publication arising from the study.

#### 2.14.4 Trial registration

This study has been registered on the Australian New Zealand Clinical Trials Registry (ANZCTR) (ID: ACTRN12619000242123; registered 19^th^ February 2019) and the International Standard Randomised Controlled Trial Number (ISRCTN) (ID: ISRCTN78951376; registered 10^th^ July 2019) prior to enrolment of the first participant.

## 3. Discussion

Emerging research indicates that increasing both the frequency and quality of social interactions may be key to maintaining healthy ageing [5]. Given the likely bidirectional relationships between social participation and emotional distress [6], interventions that enhance social participation through increased meaningful social contact, social group membership and volunteering should lead to increased quality of life, improved physical and mental health, as well as reduced mortality in older adults. By building stronger social support and increasing social contact, the maintenance of psychological intervention outcomes for older adults is also likely to be enhanced. This study seeks to evaluate the clinical efficacy and cost utility of incorporating a strong focus on social participation into a standard CBT program for older adults with clinical levels of anxiety and depression.

Participants in the enhanced CBT program will receive current best-practice transdiagnostic CBT, in addition to being actively encouraged to make new social connections and/or strengthen existing social connections. One major strength of our intervention design is that the enhanced CBT program will target maladaptive cognitions with respect to social interactions. In light of previous findings that up to half of older adults continue to experience clinically impairing symptoms of depression and anxiety following CBT [17], there are likely at least two groups of non-responders. The first is individuals who show an inadequate response at post-treatment, the second is those who initially respond to treatment but quickly relapse. In either case, poor social connectedness might be one factor related to suboptimal treatment outcomes. Loneliness research has posited that the perception of social isolation potentially increases an implicit hypervigilance for social threats, as well as biased appraisal of other people’s intentions and behaviours [40, 41]. These maladaptive biases are likely to influence an individual’s motivation to engage in social interactions [21], as well as triggering maladaptive behaviours in social situations, and social withdrawal. Further, it has been suggested that maladaptive social cognitions may be implicated in the maintenance of depression symptoms [21]. Although previous intervention studies have shown that social connectedness can be effectively improved through behavioural activation [21], educational programs [42], computer training [43], psychosocial education, or shared activities [44], maladaptive social cognitions have rarely been directly addressed in these interventions, even less so in older adult populations. Furthermore, interventions that target maladaptive social cognition have been shown to have larger effect sizes compared to interventions that enhance social support, improve social skills, or provide opportunities for social intervention [45]. Taken together, these findings underscore the potential benefits of enhancing personal motivation in facilitating greater participation, rather than just providing opportunities for social interactions.

In the current study, the intervention strategies in the enhanced CBT program are designed to increase meaningful social interactions through a combination of cognitive and behavioural techniques. Research indicates that a transdiagnostic CBT program for depression and anxiety may be effective in reducing loneliness in older adults, and that this reduction is likely to be facilitated by targeting shared underlying cognitive and behavioural mechanisms between loneliness, depression, and anxiety [20]. The current study will be testing out hypotheses around the application of CBT skills in addressing these underlying mechanisms. That is, participants in the enhanced CBT program will be encouraged to actively identify and challenge unhelpful or unrealistic cognitions related to social activities and interactions. This process is complemented by behavioural activation to encourage broader engagement in social activities, including scheduling regular activities with family and friends, participating in community group activities, and/or volunteering. Participants will also be encouraged to practise graded exposure to reduce avoidance of social interactions, as well as problem solving logistical barriers (e.g., cost and transportation). Furthermore, the enhanced CBT program will focus on improving assertiveness skills and conflict management to strengthen social relationships.

Our previous pilot data indicated that the enhanced CBT program, which incorporated a specific focus on increasing social participation in older adults, was associated with significant increases in social activities and overall quality of life, and marked reductions in symptoms and diagnoses of anxiety and depression. Furthermore, all changes were maintained at three-month follow-up and improvements in the social relationships’ component of quality of life suggested further improvement from post treatment to three-month follow-up. Participant feedback on the enhanced program was very positive. Importantly, when comparing effects from the enhanced CBT program of our pilot sample with the average results of standard CBT across our two larger RCTs [16, 17], the enhanced CBT program was associated with considerably large effects on both emotional distress and quality of life related to social relationships. Following these promising pilot data, the parallel group superiority randomised controlled trial design in this study will further evaluate the clinical efficacy of the enhanced CBT program for depressive and/or anxiety disorders in older adults, compared to the standard CBT program.

Outcomes from this study will provide evidence for an augmented psychosocial treatment for older adults suffering anxiety and/or depression. The treatment is supported by structured manuals, enabling dissemination. Bolstering meaningful social interactions in conjunction with exciting CBT skills is a novel approach to increase recovery rates for older adults suffering from depressive and anxiety disorders, as well as enhancing wellbeing and social participation in this age group, and thereby directly contributing to better economic outcomes. In addition to the empirical validation of a novel treatment, the current study will contribute to the current understanding of the role of social participation in older adult wellbeing.

### 3.1 Trial status

Recruitment commenced on 16^th^ July 2019. This study is expected to be completed by 31^st^ December 2022.
